## Abstract

**Background:**

Whiplash injury is the most common traffic-related injury affecting thousands of people every year. Conservative treatments have not proven effective in preventing persistent symptoms and disability after whiplash injury. Early established maladaptive pain behaviours within the first weeks after the injury may explain part of the transition from acute to chronic whiplash associated disorder (WAD). Hence, early targeting of psychological risk factors such as pain catastrophizing, fear-avoidance-beliefs, depression, and symptoms of posttraumatic stress disorder (PTSD) may be important in preventing the development of chronic WAD. Some evidence exists that targeting fear-avoidance beliefs and PTSD with exposure strategies and value-based actions may prevent development of persistent disability after whiplash injury. Yet, the results have to be tested in a randomized controlled trial (RCT). The primary objective of the present study is to test whether a specifically tailored value-based cognitive-behavioural therapy program (V-CBT) is able to prevent the development of persistent disability, pain, and psychological distress if delivered within the first three months after a whiplash injury.

**Methods/design:**

The current study is a two-armed randomized controlled study with a crossover design. Group A is scheduled for V-CBT within one week of randomization and group B with a delayed onset 3 months after randomization.

**Discussion:**

If the study detects significant effects of V-CBT as a preventive intervention, the study will provide new insights of preventive treatment for patients with WAD and thereby serve as an important step towards preventing the chronic condition.

**Trial registration:**

Current Controlled Trials Registration September 19, 2014: NCT02251028

## Background

In Denmark, it is estimated that around 6.000 individuals are exposed to a whiplash trauma every year [1]. Up to 50 % are still experiencing neck pain and disability one year after the incidence [2], and 13 % are disabled to such a degree that they are partly or fully unable to maintain work [3, 4]. Although some evidence exists, that high-intensity strength training may reduce neck pain among industrial workers [5], conservative treatments (analgesics, physiotherapy, and instructions on exercises) have not proven effective in preventing persistent symptoms and disability after whiplash injury [6].

The common recovery process after the injury appears to follow a pattern of rapid improvement within the first three months, with only minor, if any, improvement thereafter [7]. Early established maladaptive pain behaviours within the first weeks after the injury may explain part of the transition from acute to chronic pain. The fear-avoidance model [8, 9] describes how painful stimuli may trigger catastrophic thinking and how fear-avoidance-beliefs ultimately lead to avoidance behaviour, more pain, and depressive thinking. Recently, PTSD has been emphasized as a significant risk factor for the development of chronic pain and disability after a whiplash trauma [7, 10, 11], and a high prevalence of PTSD (15–38 %) has been found among those who have encountered a whiplash trauma [7, 12–14]. PTSD and chronic pain is presumed to maintain one another through an array of cognitive and behavioural mechanisms such as increased hypervigilance, catastrophizing, and avoidance [15, 16]. Hence, early targeting of these psychological risk factors may be important in preventing the development of chronic WAD.

In this regard, promising preliminary support for targeting fear-avoidance behaviour is found in two recent studies successfully treating PTSD [17] and fear of movement in relation to WAD [18]. Both studies achieved clinically significant improvement of PTSD symptoms, pain, and disability. In addition, to exposure-based strategies and CBT techniques, Wicksell and colleagues [19] found that an intervention specifically targeting functional restoration by increasing chronic whiplash injured patients’ willingness to engage in activities in accordance with their life goals and values, significantly improved daily life functioning and life satisfaction compared to a wait-list control group.

Finally, some evidence exists that early intervention, aimed at patients with high levels of perceived disability, pain catastrophizing, and fear-avoidance beliefs, can prevent exclusion from the labour market [20–22]. The greatest success rate of return to work was achieved by intervening between 4 to 12 weeks after the whiplash trauma, indicating that early intervention is important [20]. However, to date no RCT study has used a combined intervention comprising value-based actions and exposure strategies in preventing persistent pain and disability after sub-acute whiplash injury.

### Aims and hypotheses

The aim of the present study was twofold: 1) to test whether a specifically tailored value-based cognitive-behavioural therapy program (V-CBT) delivered within the first three months after whiplash injury can prevent the development of chronic WAD compared to the wait-list controls at 6 months post-randomization and 2) to investigate whether there exists a 3-months window for preventing chronic pain, disability, and psychological distress after a whiplash injury.

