### Participants

All participants are between the age of 18 and 65-years old and are diagnosed with WAD grade I-II [23]. At 3-months post injury, they are experiencing disability in at least one important life domain (≥5 on the pain disability index) and moderate levels of pain (average pain intensity ≥ 4 on the NRS scale). Also, they have to meet at least one of the psychological risk criteria: elevated levels of pain catastrophizing, fear-avoidance beliefs, symptoms of anxiety and/or depression, and posttraumatic stress symptoms). Clinically relevant cut-off score criteria are based on previous studies [21, 24, 25]. Criteria of exclusion is treatment for other damages sustained in connection with the whiplash trauma, psychiatric disorders, active abuses of alcohol, drugs, or medication, ongoing rehabilitation or other treatment for pain besides physiotherapy and pharmacological treatment, and non-Danish speaking.

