### Randomization and blinding

Patients are randomized by random permuted blocks of 4 to 8 by the study statistician at University of Southern Denmark. Randomization is consecutively numbered in sealed opaque envelopes. Patients will randomly be allocated to one of two treatment groups (A or B) in a crossover design with both groups receiving the V-CBT intervention, however with a delayed onset for group B. Group A is scheduled for V-CBT within one week of randomization and group B with a delayed onset of 3-months after randomization. Measurements of effect are carried out at baseline before randomization (3 months post-injury), post-treatment/wait-list (3 months post randomization), and at follow-up (9 months post randomization/12 months post-injury). At all time points patients are asked which potential additional treatment they have received. The clinical psychologists are not blinded to which intervention the patients receive. However, at the point of analysis, the two groups will be coded as X and Y in order to blind the researcher who will conduct analysis.

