### Sample size and statistical analysis

To our knowledge no similar studies have been conducted. For this reason, the power calculation is estimated according to the earlier studies using CBT and acceptance-based strategies with functional restoration and activity engagement as their primary goal. From these earlier results, a moderate effect size is to be expected (η_p_^2^ = 0.25) [19, 20]. By putting the level of significance at 5 %, the power at 80 %, and the expected dropout at 9 months post-randomization to be 10 %, it is calculated that there should be 40 patients in each group (A & B).

The primary and secondary outcomes measured for both groups at baseline before randomization (3 months post-injury), 3 months post-randomization, and 9 months post randomization (12 months post-injury) will be analysed using linear mixed-effects models (random coefficient models and multilevel models). With the mixed effects model approach all available data will be used and intention-to-treat analyses applied.

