## Discussion

The primary objective of the present study is to test whether the specifically tailored V-CBT program is able to prevent the development of persistent disability, pain, and psychological distress if delivered within the first three months after a whiplash injury. In particular, early identification and targeting of fear-avoidance beliefs, pain catastrophizing, and symptoms of PTSD seem to be of importance.

In contrast to symptom reduction, aiming to improve functioning and activity engagement in patients has shown promising results [18, 19, 29]. In particular, the combination of exposure and value-based strategies for functional restoration may be important. Also, addressing PTSD symptomatology seems essential in relation to functional restoration [17]. Based on learning theory [9, 27], maladaptive pain behaviours may develop within the fist weeks after an injury, why early intervention may prevent this maladaptive pattern. Indeed, this is indicated by Adams and Colleagues [20], finding their intervention most effective when delivered within three months after the whiplash injury. However, research has yet to determine in a RCT study whether targeting these early risk factors will prevent long-term disability and psychological distress. Also, it is important to gain knowledge whether there exists a 3-months window for intervention, as indicated by longitudinal cohort studies of recovery after whiplash injury [7].

Whiplash injury is the most common injury after traffic accidents and represents a major societal and personal problem. For this reason, if effective, the intervention program will have significant importance for both patients and the society. Moreover, the program can easy be implement in already established pain clinics around the country. In the present study no health economic analyses are planned. However, recently a study by Kemani and colleagues [39] showed that acceptance and commitment therapy for longstanding pain was more cost-effective than an active control treatment. The present study could be strengthened by a register study of the long-term health-economic effects of the V-CBT program.

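### The aims place V-CBT within three months of injury, but the schedule compares a start at about month 3 with a start at about month 6

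*Protocol article*

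**What the plan says.** Three statements of purpose in the protocol article count time from the injury:

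- Aim 1 (Aims and hypotheses) tests whether V-CBT "delivered within the first three months after whiplash injury can prevent the development of chronic WAD".
- The primary objective concerns prevention "if delivered within the first three months after a whiplash injury" (Abstract, Background), and the Discussion repeats it: "psychological distress if delivered within the first three months after a whiplash injury".
- Aim 2 asks "whether there exists a 3-months window for preventing chronic pain, disability, and psychological distress after a whiplash injury".

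The Methods set the calendar:

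- Participants: "At 3-months post injury, they are experiencing disability in at least one important life domain".
- Randomization and blinding: "Measurements of effect are carried out at baseline before randomization (3 months post-injury").
- Sample size and statistical analysis: the last visit is at "9 months post randomization (12 months post-injury").
- Randomization and blinding: "Group A is scheduled for V-CBT within one week of randomization and group B with a delayed onset of 3-months after randomization".
- Intervention: ten weekly one-hour sessions.
- Enrolment: recruitment takes place 2 to 3 months after the injury.

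**The concern.** If randomization happens at month 3 and treatment follows it, the early arm is treated after the period that the aims name. Month 3 is not an incidental figure here. The Background describes rapid recovery up to that point and little afterwards, and cites the best return-to-work results for intervention at 4 to 12 weeks. Aim 2 is built on that boundary.

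What is at stake is the conclusion the trial may draw. A reader of the results could take them as evidence about treatment in the first three months after injury, or about whether an opportunity closes at month 3. On the stated schedule the trial provides neither.

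**Working it through.** **Inputs.** Follow-up at 9 months post-randomization, equal to 12 months post-injury. Group A starts 0 to 1 week after randomization and group B 3 months after it. There are ten weekly sessions, so 9 weeks from first to last. Conversion: 1 month = 4.348 weeks.

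**The plan's own figure first.** Randomization = 12 - 9 = 3 months post-injury. This agrees with the stated baseline.

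**Length of the programme.** 9 / 4.348 = 2.07 months. A one-week delay is 1 / 4.348 = 0.23 months.

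**Timeline in months post-injury.** With randomization at time r:

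- group A first session = r to r + 0.23
- group A last session = first session + 2.07
- group B first session = r + 3, last session = r + 5.07

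The Methods give r = 3.0. The rows for 2.5 and 2.0 are a sensitivity range, on the assumption that the recruitment period in Enrolment also governs the date of randomization.

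| r | A first session | A last session | A sessions by month 3 | B first to last |
|---|---|---|---|---|
| 3.0 | 3.00-3.23 | 5.07-5.30 | 0-1 of 10 | 6.00-8.07 |
| 2.5 | 2.50-2.73 | 4.57-4.80 | 2-3 of 10 | 5.50-7.57 |
| 2.0 | 2.00-2.23 | 4.07-4.30 | 4-5 of 10 | 5.00-7.07 |

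**Could anyone finish by month 3?** The latest workable randomization is 3 - 2.07 = 0.93 months with a same-day start, or 0.93 - 0.23 = 0.70 months with a one-week delay. Both come before recruitment opens at 2 months.

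**Against the cited 4 to 12 weeks.** Month 3 is week 3 x 4.348 = 13.0, so group A starts at weeks 13.0-14.0 on the stated schedule. In the earliest case it starts at weeks 8.7-9.7 (2 x 4.348 = 8.7).

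**What the contrast can show.** The two start times lie 3.00 - 0.23 = 2.77 to 3.00 months apart whatever r is, with no start tested between them. A difference between arms would fit a cut-off anywhere in that gap, or a gradual decline with no cut-off. On the stated schedule, a null result would not refute a window closing at month 3, because both arms start at or after that point.

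**The other date in Aim 1.** Its sentence places the wait-list comparison 6 months post-randomization. The listed visits are baseline, 3 months and 9 months post-randomization. Group B's sessions run from 3.00 to 5.07 months after randomization, so at 6 months it is no longer an untreated control. The listed visit at which it still is one falls 3 months post-randomization, which is 3 + 3 = 6 months post-injury.

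**The case against.** The strongest reply is that delivery within three months means starting within three months. The article describes its arms by onset, and its rationale is about when one intervenes. Recruitment at 2 to 3 months could then put some group A starts before month 3, if the 3-month baseline is a rounded label for the end of that period. This part stands: on the start reading, the mismatch depends on when patients are actually randomized. A reader might infer that no patient can be treated inside the window on any reading. The documents do not support that; it is certain only for completion. What remains is that eligibility, baseline and follow-up are all dated from a nominal month 3, and Enrolment places a letter, a pain rating, a telephone screen, a mailed questionnaire and a consultation before randomization.

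A second reply is that the three months count from randomization. This works for hypothesis 2, since group A finishes 2.07-2.30 months after randomization. It does not work for Aim 1, Aim 2 or the primary objective, which name the injury.

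A third reply is that Aim 2 only proposes to investigate a window, and that any two-arm trial of early versus delayed treatment has just two start times. That is a fair limit on inference and not in itself an error. The problem is that Aim 2 fixes the window at three months after injury, and the two start times do not bracket that point on the stated schedule.

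**Conclusion.** The point holds as a mismatch between the stated aims and the stated schedule. With randomization at month 3, at most 1 of group A's 10 sessions falls by that date, and treatment runs from about month 3 to 5 in group A and about month 6 to 8 in group B. Completion by month 3 is impossible for every patient recruited as described. A start before month 3 is possible only for patients randomized early in the recruitment period; in the extreme case of randomization at 2.0 months, 4-5 of 10 sessions would fall by month 3.

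A reader might go further and infer that the trial's comparisons are undermined. They are not. V-CBT versus wait-list at 3 months post-randomization, and an earlier versus a three-month-delayed start at follow-up, are both sound randomized contrasts. What fails is the claim that they bear on a window closing three months after injury.

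The figures assume weekly sessions without gaps and treat the visit labels as nominal, so actual dates will vary around them.

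**What to change.** Change the wording, not the design:

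- **Aim 1 and the primary objective (Abstract and Discussion):** describe V-CBT started about 3 months after injury. If Enrolment's 2 to 3 months is meant to govern randomization, say 2 to 3 months and bring Participants and Randomization and blinding into line.
- **Same Aim 1 sentence:** move the wait-list comparison to the listed visit at 3 months post-randomization (6 months post-injury).
- **Aim 2:** compare a start at about 3 months with a start at about 6 months post-injury.
- **Hypothesis 2:** state that its first 3 months are counted after randomization.
- **Reporting:** do not present the result as evidence for or against a window closing at month 3.

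Randomization, visits, outcomes and the mixed model stay as they are. The cost is a few sentences of rewording and a narrower claim.

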### Hypotheses

First, we hypothesize that there will be a significant reduction in the primary and secondary outcomes (disability, pain, and psychological distress) in the V-CBT group (group A) compared to the wait-list controls (group B). Secondly, we hypothesize that the largest effect will be achieved by early intervention within the first 3 months compared with the group receiving treatment after 3 months of waiting. Finally, we expect that these effects will be maintained at a 9 months follow-up post-randomization (12 months post-injury).

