## Methods

The current study is a two-armed RCT study with a crossover design. Both groups will receive treatment. Group A is scheduled for V-CBT within one week of randomization and group B with a delayed onset 3 months after randomization. See Fig. 1 flow diagram.

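### The effect of V-CBT over wait-list can be tested only at 3 months post-randomization; Aim 1's 6-month comparison and the matching part of hypothesis 3 at 9 months have no untreated control

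*Protocol article*

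**What the plan says.** All references are to the protocol article.

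- **Methods:** "The current study is a two-armed RCT study with a crossover design. Both groups will receive treatment". The timing is: "Group A is scheduled for V-CBT within one week of randomization and group B with a delayed onset 3 months after randomization".
- **Intervention:** the program is 10 weekly individual sessions.
- **Randomization and blinding; Sample size and statistical analysis:** outcomes are measured at baseline (3 months post-injury), at 3 months and at 9 months post-randomization. Linear mixed-effects models use these three time points under intention to treat.
- **Aims and hypotheses:** Aim 1 is to test whether V-CBT "can prevent the development of chronic WAD compared to the wait-list controls at 6 months post-randomization". Aim 2 asks whether there is a 3-month window for prevention.
- **Hypotheses:** the first predicts a reduction in outcomes "in the V-CBT group (group A) compared to the wait-list controls (group B"). The second predicts the largest effect from early treatment, "compared with the group receiving treatment after 3 months of waiting". The third adds that "we expect that these effects will be maintained at a 9 months follow-up post-randomization (12 months post-injury").
- **Discussion:** the primary objective is to test whether the program can "prevent the development of persistent disability, pain, and psychological distress if delivered within the first three months after a whiplash injury".

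**The concern.** The third hypothesis carries two different effects forward to 9 months: the advantage over waiting and the advantage of early over delayed treatment. Only the second still has its comparator at that time. Aim 1 names a wait-list comparator at a time when the wait-list group has been treated.

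What is at stake is how the results are read. Under the present wording, no difference between A and B at 9 months could be reported as a lost effect, although it may mean that B caught up. A difference could be reported as a maintained effect over no V-CBT, although it shows only that early and delayed treatment differ. Either reading would bear on the prevention claim, which is the stated primary objective.

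**Working it through.** **Step 1. Treatment status at each time point.** The inputs are the start times in Methods, the 10 weekly sessions in Intervention, and the visits in Randomization and blinding. Ten weeks are about 2.3 months, so B's course runs from about month 3 to about month 3 + 2.3 = 5.3.

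| Months post-randomization | Months post-injury | Group A | Group B | Measurement planned | What A minus B compares |
|---|---|---|---|---|---|
| 3 | 6 | treated | waiting | yes | V-CBT with waiting |
| 6 | 9 | treated | treated as scheduled | no | early with delayed V-CBT |
| 9 | 12 | treated | treated | yes | early with delayed V-CBT |

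**Step 2. What the 9-month difference identifies.** Let E be the effect of early V-CBT still present at 9 months and L the effect of delayed V-CBT at 9 months, each relative to no V-CBT. Then

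A minus B at 9 months = E − L.

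Randomization supplies this one contrast. No arm supplies E or L alone.

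**Step 3. Scale.** The article's effect size is partial eta squared 0.25, which gives f = sqrt(0.25/0.75) = 0.577 and, for two groups, a standardized difference d = 2f = 1.155. (With these inputs a two-group comparison of means needs 12 per group, or 14 after 10 % dropout, so the stated 40 is not reproduced. That is a separate matter and does not affect this point.)

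With effects on this scale:

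- E = 1.155, L = 1.155: difference 0. Full maintenance, full catch-up.
- E = 0, L = 0: difference 0. Effect lost in A, none in B.
- E = 1.155, L = 0.577: difference about 0.577. Full maintenance, half catch-up.
- E = 0.577, L = 0: difference 0.577. Half of A's effect lost, no benefit from delayed treatment.

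Within each pair the expected data on A minus B are the same, while the answer on maintenance over waiting is opposite or very different.

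**Step 4. How far the 9-month contrast depends on B.** Assumptions: 36 evaluable per arm (40 less 10 %), two-sided 5 %, A keeps its full effect, and B gains a share s of it. The normal approximation, counting rejections in favour of early treatment, is

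power = Φ(d × (1 − s) × sqrt(36/2) − 1.96).

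Example at d = 1.155, s = 0.5: 0.577 × 4.243 − 1.96 = 0.49, and Φ(0.49) = 68.8 %.

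| | d = 1.155 (from the article) | d = 0.5 (assumption) |
|---|---|---|
| Month 3, B untreated | 99.8 % | 56.4 % |
| Month 9, B gains 25 % | 95.7 % | 35.6 % |
| Month 9, B gains 50 % | 68.8 % | 18.4 % |
| Month 9, B gains 75 % | 23.1 % | 7.6 % |
| Month 9, B gains 100 % | 2.5 % (5 % counting both directions) | same |

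A's effect is perfectly maintained in every month-9 row. The chance of a significant contrast moves only with what happens in B.

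**The case against.** Several arguments on the other side are sound.

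- **Hypothesis 3 is not untestable as a whole.** A reader might infer that it is. It refers to effects in the plural, and one of them is early versus delayed V-CBT, which is also Aim 2. The randomised 9-month contrast tests exactly that. This stands.
- **The 3-month comparison is valid.** A reader might infer that the trial has no controlled evidence on persistent disability or pain. It has, at 6 months post-injury. The article sets no time threshold for chronic WAD, so whether that counts as prevention is open. The missing threshold is a side issue and changes no result.
- **Full catch-up is not what the article predicts.** A reader might infer that the trial fails in the very outcome its sponsor hopes for. Hypothesis 2 expects early treatment to do best, so under it a difference remains at 9 months. A zero difference with full maintenance arises only if hypothesis 2 is false. This stands, and it is why a range is shown above.
- **No specific maintenance test is stated.** The article does not say that maintenance will be judged by A minus B at 9 months, and its mixed models can give the change within group A. The choice of contrast may properly be left to an analysis plan. This stands too, but it does not rescue the wording: an analysis plan can choose a contrast, yet it cannot supply an untreated comparator after month 3.
- **The crossover label.** A reader might infer that it conceals the problem or implies a within-patient comparison. The delayed start is explained wherever the label appears and no within-patient crossover analysis is planned, so no estimate depends on it.

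**Conclusion.** The point holds in a limited form. By randomised comparison, the effect of V-CBT over wait-list can be tested only at 3 months post-randomization (6 months post-injury). At 9 months the effect over wait-list is not identified, and the A-versus-B contrast answers only whether early differs from delayed V-CBT. Aim 1's comparison at 6 months post-randomization lacks both an untreated control and a planned measurement.

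This conclusion follows from the schedule and needs no effect size. It assumes that group B is treated broadly as scheduled. The power figures are illustrations: they rest on 36 evaluable per arm, full maintenance in A, and an effect of either 1.155 (converted from the article's value) or 0.5 (assumed). The documents do not support saying that the 9-month data are uninformative or that the early-versus-delayed question cannot be answered.

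**What to change.** Change the wording in four places:

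1. Set Aim 1 and hypothesis 1 at 3 months post-randomization, group A against the wait-list. This uses a measurement already planned. If Aim 1's 6 months was meant as time since injury, this is the same visit (3 + 3 months), and the text should say so.
2. Define the 9-month A-versus-B contrast as early versus delayed V-CBT only, serving hypothesis 2 and Aim 2.
3. Restate the rest of hypothesis 3 as the change in mean PDI within group A from 3 to 9 months, with a 95 % confidence interval, labelled non-randomised.
4. Limit any claim of effect over waiting, or of prevention, to 6 months post-injury.

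No visit, patient or model needs to be added, since the planned mixed models can yield these quantities. The cost is a narrower prevention claim: the trial would no longer claim a controlled effect against no V-CBT at 12 months post-injury.
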